**Outcome**	
3rd next available appointment (weekly)	Number of days before the 3rd next available appointment open for general consultation
Relational continuity (monthly)	Total number of medical consultations with a patient’s attached family physician (or specialised nurse) out of the total number of consultations with any family physician (or specialised nurse) from the clinic. Evaluates relational continuity between the provider and their registered patients
**Process**	
48-h capacity (weekly)	Proportion of appointments available in the next 48 h. Provides an overview of the provider’s ability to respond to urgent care demands
Use of walk-in clinics (monthly)	Proportion of consultations with registered patients offered through walk-in visits out of the total number of consultations with their attached professional
Professional diversity of care (monthly)	Proportion of consultations with a physician, resident or specialised nurse out of the total number of consultations with any provider at the clinic. Evaluates the level of involvement of different types of providers (social workers, nurses, pharmacists, etc.) with registered patients
14-day capacity (weekly)	Proportion of appointments available in the next 14 days. Provides an overview of the provider’s ability to respond to routine care and follow-up demands
**Balancing**	
Discontinued care for patients with chronic disease (monthly)	Proportion of registered patients with at least one chronic condition who have not consulted the clinic within the last 12 months

The proposed CQI intervention present in Fig. 3 consists of three activities carried out iteratively until the improvement objectives are achieved or up to a maximum of 18 months of intervention: 1) team reflection and prioritisation of change needs; 2) PDSA cycles; and 3) group mentoring.

**Fig. 3 Fig3:**
[figure not shown]
The CQI cohorts

### Activity 1: reflective sessions and problem prioritisation

An essential condition for people to become involved in improvement initiatives is that they arrive at a shared understanding of the issues to be solved or the challenges to be overcome, which requires a strong commitment from the participants [20, 75–77]. Participants in the CQI intervention need to *understand the problem and its root causes and contributing factors *[58]. To this end, we will organise clinic-wide meetings labeled *reflective sessions*. These face-to-face sessions, led by the research team and a QI coach, will involve all team members at a given clinic, including clinical, administrative and management staff. During these sessions, we will identify and prioritise AA-related issues. To do so, a summary of AA processes and outcomes will be presented to the group. These will be populated with a comprehensive assessment of both AA processes (using ORAA questionnaires [18]) and outcomes (from the clinic’s electronic medical record [EMR] data and patient-reported experiences of access; see Data collection section below). Through customised facilitation activities, participants will be asked to generate and prioritise ideas to improve AA while considering the concerns of all team members. These activities will maximise engagement of team members and foster discussions and collaboration among them. Examples of facilitated activities include brainstorming sessions, design thinking sessions, root-to-cause analysis and any other activities that might address the specific AA-related issues faced by the team [78]. The end result of Activity 1 consists of an improvement aim [79] focused on a particular AA pillar, identifying the goal(s) the team would like to achieve before the next reflective session, who will benefit from this improvement, how change will be measured and by when.

### Activity 2: PDSA cycles

Following the reflective sessions, we will identify a QI team from each clinic, comprised of at least one team member from all categories of staff (e.g. physicians, nurses, administrative staff, other PHC providers, patients) for a maximum of 5–8 individuals. Each member of the QI team will have the responsibility, through PDSA cycles, to reach the aim(s) determined during Activity 1. Supported by the lead research team, they will convene (every 2 to 4 weeks for approximately 30 min) to review the clinic’s aims (first meeting), then develop (Plan) and implement changes (Do), monitor the effect of these changes on key AA measures (Study) and review the process in order to maintain changes or adjust future actions (Act) [80, 81]. These meetings will take place virtually. More frequent meetings will be organised as needed if the pace of the cycles requires it.

### Activity 3: group mentoring

As teams engage in PDSA cycles, they will test change strategies and generate knowledge about strategies that do or do not work in their specific context [20]. This knowledge will be documented in change packages that include a clear description of the strategy, the indicators used to evaluate its impact, lessons learned and a sustainability plan [60]. These packages have been reported as being highly valuable in supporting organisational change [63, 82]. Group mentoring will aim to increase the effectiveness of the QI coach’s follow-ups and to optimise knowledge transfer of AA improvement strategies among clinics. The first part of the meetings will consist of continued education material about AA- and CQI-related theories and will be provided by the three QI coaches recruited for the trial. Then, participants will split into groups based on their respective AA pillars of focus. A member of each QI team will be invited to share their learnings from the ongoing PSDA cycles (change strategies adopted, lessons learned, indicators used, data extraction algorithms from the EMR). These exchanges will help improve the change packages for each of the AA pillars. These virtual meetings will be held every 6–8 weeks.

Once an improvement aim has been achieved (expected after 3–9 months), the PHC clinic members will reconvene for another reflective session. The QI team will present the changes implemented during the cycles. These sessions will provide a regular meeting place for all team members to voice their concerns and ideas, which can then be used by the QI team during subsequent PDSA cycles. Depending on their new improvement aim (and associated pillar), the QI team will be invited to join an ongoing mentoring group or to form a new one.

### Recruitment

Forty-eight multidisciplinary PHC clinics will be recruited in close collaboration with our key stakeholders using voluntarism and purposeful sampling, with the objective of covering a wide range of organisational structures and contexts, including geographical and socioeconomic differences. To be recruited, clinics must offer interprofessional care (beyond the physician-nurse only model) that is physically located under the same roof. To take part of the study, team member should sign the electronic inform consent form, and at for the PHC clinics at least 50% of all team members should accept to take part in the study to be eligible.

### Sample size justification

The Quebec CQI pilot project showed that the average time to the 3rd next available appointment (primary outcome) is 11 days (sd = 10). Forty-eight clinics (clusters) averaging 15 professionals per clinic for a total of 720 professionals over six measurement time points will be measured every week or month (depending on the measure). An assumed intracluster correlation (ICC) of 0.364 (from the pilot project) provides about 80% power to detect a small effect size of 0.25 (Cohen’s d, assuming that variation will increase over the course of the intervention). This translates into a 50% reduction in time to the 3rd next available appointment from the baseline assessment [83]. Variations in clinic size have been considered (coefficient of variation of 0.49 according to the pilot project) [84]. No inflation for loss to follow-up is planned because the data is readily obtained from the EMR system for all professionals. Provision for one interim analysis 12-months post recruitment is planned using the Demets and Lan’s alpha spending function approach [85]. Thus, we aim to recruit 48 PHC clinics (24 interventions and 24 controls) for the trial proposed in this study.

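### The sample-size statement cannot be reproduced from its own inputs: at mean 11 and SD 10, d = 0.25 is a 23% reduction, not 50%, and the 80% power at d = 0.25 rests on correlations that are not given

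*Protocol article*

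**What the plan says.** All the figures stand in the Protocol article under Sample size justification.

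- Pilot distribution of the primary outcome: "the average time to the 3rd next available appointment (primary outcome) is 11 days (sd = 10").
- Size and structure: "Forty-eight clinics (clusters) averaging 15 professionals per clinic for a total of 720 professionals over six measurement time points", split 24 and 24.
- Clustering: "An assumed intracluster correlation (ICC) of 0.364 (from the pilot project"), and variation in clinic size with a "coefficient of variation of 0.49 according to the pilot project".
- Claim: the design "provides about 80% power to detect a small effect size of 0.25" on Cohen's scale, "assuming that variation will increase over the course of the intervention".
- Translation into days: "This translates into a 50% reduction in time to the 3rd next available appointment from the baseline assessment".

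The paragraph gives no inflated SD, no significance level, no correlation over time, and no split of the six time points into before and after. The Data analyses section plans a mixed model for the primary outcome, adjusted for time. The Data collection section commits to at least three months of data before the intervention starts, and names the intervention clinics only.

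**The concern.** The paragraph describes one target effect in two ways, as a small standardised difference and as a halving of waiting time. With the printed mean and SD these are different effects, one more than twice the other. The power claim is attached to the smaller one, yet with an ICC as high as 0.364 and 24 clinics per arm a simple comparison of arms cannot detect so small a difference reliably.

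This paragraph is the article's only justification for 48 clinics. As printed, a reader cannot tell whether the trial was sized for 2.5 days or 5.5 days, or which analysis the 80% belongs to. That matters when the width of the final confidence interval is judged against the planned effect.

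**Working it through.** **Inputs (Sample size justification):** mean 11 days, SD 10, 24 clinics per arm, m = 15 professionals per clinic (360 per arm), ICC 0.364, CV of clinic size 0.49. **Assumed:** two-sided 5%, since no level is printed.

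**1. Effect size.** Reduction = d × SD / mean.
- d = 0.25: 0.25 × 10 = 2.5 days; 2.5 / 11 = 23%.
- 50%: 5.5 days; 5.5 / 10 gives d = 0.55.
- SD at which both hold: 5.5 / 0.25 = 22 days, 2.2 times the pilot value.

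**2. Attempt to reproduce the 80%: one comparison of arms at follow-up.** Design effect = 1 + [(1 + CV²)m − 1] × ICC; effective n per arm = 360 / design effect; z = d × √(effective n / 2); power = Φ(z − 1.96).
- With CV 0.49: design effect = 1 + (18.60 − 1) × 0.364 = 7.41; effective n = 48.6. At d = 0.25, z = 1.23 and power is 23%. At d = 0.55, z = 2.71 and power is 77%.
- With equal sizes: design effect = 1 + 14 × 0.364 = 6.10; effective n = 59.1. Power is 27% at d = 0.25 and 85% at d = 0.55.
- Upper limit with unlimited professionals per clinic: standard error = √(2 × 0.364 / 24) = 0.174; power at d = 0.25 is 30%.
- Detectable d at 80% power: 0.57 with CV 0.49, 0.52 with equal sizes.

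The stated 80% at d = 0.25 is not reproduced.

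**3. Does a larger SD rescue it?** Power for a 50% reduction in the same calculation:

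| SD (days) | d for 5.5 days | Power, CV 0.49 | Power, equal sizes |
|---|---|---|---|
| 10 | 0.55 | 77% | 85% |
| 15 | 0.37 | 44% | 51% |
| 22 | 0.25 | 23% | 27% |

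At SD 10, 50% and roughly 80% fit each other but d is not 0.25. At SD 22, 0.25 and 50% fit but power does not. No SD satisfies all three.

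**4. Do the six time points rescue it?** Assume equal sizes, clinic autocorrelation c, and provider autocorrelation t varied over 0, 0.5 and 0.8. With a periods before and b after, and standard error √(2V / 24):
- Difference-in-differences: V = [ICC(1 − c) + (1 − ICC)(1 − t)/m] × (1/a + 1/b).
- Baseline means constrained equal: V = var(post mean) − cov² / var(pre mean), where cov = ICC × c + (1 − ICC)t/m and the variance of a mean over T periods is ICC[c + (1 − c)/T] + (1 − ICC)[t + (1 − t)/T]/m.

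Example (a = 1, b = 5, c = 0.8, t = 0): difference-in-differences V = (0.0728 + 0.0424) × 1.2 = 0.138, z = 2.33, power 64%. Constrained V = 0.3142 − 0.2912² / 0.4064 = 0.1056, z = 2.67, power 76%.

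Power at d = 0.25, ranges over t:

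| Clinic autocorrelation | Six post only | 1 pre + 5 post, difference-in-differences | 1 pre + 5 post, constrained baseline |
|---|---|---|---|
| 0.5 | 41–46% | 38–44% | 62–64% |
| 0.8 | 32–34% | 64–79% | 76–86% |
| 0.9 | 30–32% | 80–96% | 87–98% |
| 1 | 28–30% | 97% or more | 98% or more |

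Six follow-up measurements alone come near 80% only if clinic effects hardly persist from one period to the next: 80–91% at c = 0, already 68–79% at c = 0.1. That is not a natural assumption for a clinic's waiting time.

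**The case against.** The strongest reply is that the trial is longitudinal. The paragraph counts six time points and measures change from baseline, Table 1 collects the outcome weekly, and the analysis is a mixed model over time. A reader might infer from step 2 that the trial has 23% power, or that it is powered only for a halving. The documents do not support either reading. The 23% belongs to a single follow-up comparison, and step 4 shows values from about 38% to over 95% with one period before and five after, depending on correlations and on how baseline is handled. This part of the reply stands.

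A second reply is that the article does say variation will rise. That is fair, and an SD of 22 would reconcile d with 50%. But no figure is given, and step 3 shows that this repair moves the follow-up calculation further from 80%. It is also tempting to argue that the quasi-Poisson model makes variance fall with the mean. That does not settle the matter: dispersion need not stay at its pilot value, and uneven response between clinics can raise total variation.

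A third reply concerns baseline data. A reader might infer that control clinics have none. The Data collection section only names the intervention group in its commitment. It does not exclude controls, and the electronic record could supply the data. What stands is that such data in both arms are not stated, although the 80% would depend on them.

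Finally, the calculation may lie in the cited references, which are not at hand. That would explain the figures, but it would not make those printed here agree.

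**Conclusion.** The concern holds as a failure to reproduce. The effect-size mismatch depends on nothing beyond the printed mean and SD: 23% against 50%, or d = 0.25 against d = 0.55, bridged only by an unstated SD of 22 days.

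On power, the stated inputs give 23–27% at d = 0.25 and 77–85% at d = 0.55 for a follow-up comparison, assuming a two-sided 5% test and a normal approximation. So 48 clinics, about 80% and a halving roughly fit each other at SD 10, and 0.25 is the figure that does not belong with them in that calculation. The documents cannot show which figure was the slip.

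About 80% at d = 0.25 remains attainable with pre-intervention data in both arms and clinic autocorrelation of roughly 0.8 to 0.9 or more (one period before, five after, equal sizes). More pre-intervention periods would lower that requirement, and unequal clinic sizes are not allowed for in those figures. The claim is unsupported as printed; it is not shown to be false.

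**What to change.** Rewrite the paragraph so that its figures agree, in one of two ways.

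1. State the target as 5.5 days (50%), d = 0.55 at SD 10, with about 77% power for a follow-up comparison at ICC 0.364 and CV 0.49, and delete d = 0.25. Say that this calculation takes no credit for the longitudinal model.
2. Keep d = 0.25, state the SD it assumes and the reduction that follows (23% at SD 10; 50% only at SD 22), and give the baseline-adjusted repeated-measures calculation. That means the significance level, the number of periods before and after in both arms, the handling of baseline, and the clinic and provider autocorrelations. Restate the power if it falls below 80%.

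In either case, replace the remark on rising variation with a number or remove it. Under option 2, also confirm in Data collection that control clinics supply pre-intervention data.

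The cost is one reworded paragraph and no additional clinics. The stated detectable effect or power may become less favourable.

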### Data collection

Complementary qualitative and quantitative data will be collected over a period of 24 months. To evaluate the proposed trial objectives, data collection will be extended by 12 months *in the intervention group only*. We will collect data from all clinics in the intervention group for at least 3 months prior to the start of the intervention.

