## Methods

Based on the findings of other large-scale CQI initiatives [72], this study will be based on a quasi-randomised cluster-controlled trial allowing for a comprehensive and rigorous evaluation of the proposed intervention [73]. Such a design has been used to better understand both processes and outcomes of CQI [51]. Within the province of Quebec, clinics from randomly selected health regions will receive the intervention, while others will serve as controls (no CQI intervention). Intervention clinics will be matched with control clinics. The matching will be based on the clinic level (1 to 10, based on the number of patients registered and services offered) [74]. Clinics in the control group will receive an audit on a selection of AA indicators (Table 1) and will be offered the intervention 12 to 18 months following their recruitment.

**Table 1 Tab1:** Definition of AA measures

Measure	Definition

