The impact of the intervention on AA outcomes (Obj. 3) will be structured around the quintuple aim [116]. For all outcomes, we will describe clinics and participants using means and standard deviations or medians and interquartile ranges. Also, time series analyses will be performed based on EMR indicators to detect changes since baseline, at the beginning of the intervention (T3), during the intervention (T3–T18) and the sustainability of the changes (T30). *Care team functioning*: To account for clustering of providers within clinics, the primary outcome measure, 3rd next available appointment, will be analysed using a generalised linear mixed model (with log link and quasi-Poisson distribution) adjusting for time to account for secular trends as well as important contextual factors such as number of providers and readiness for change. We will inspect missing data, and if more than 10% of the sample has missing values, we will use multiple imputation techniques. Otherwise, the maximum-likelihood method of estimation is considered adequate to address missing data in such regression models [117, 118]. Differences between the control and intervention periods and time trends will be estimated using odds ratios and their 95% confidence intervals. Similar regression models will be used (as dictated by the distribution of the data) to assess differences in % of 48-h open slots, walk-in usage, relational continuity and multidisciplinary involvement. *Patient experience*: A comprehensive description of patients’ experiences will be generated three times over the study. Items that focus on ease of access, perception of interprofessional collaboration, satisfaction with the appointment process and consultations outside the clinic for non-urgent care will be used for longitudinal analysis purposes. *Population health*: Discontinuity for chronic patients will be analysed using a generalised linear mixed model to assess the impact of the project on the management of chronic patients. *Health equity and inclusion*: Accessibility and patient experience will be stratified by visible minority status, ethnicity, preferred language, gender and physical or mental ability. If any disparity seems apparent, this issue will be addressed during the improvement efforts. *Efficiency:* Total costs to the system related to the implementation of the intervention as well as costs per clinic and cohort, accounting for different organisational characteristics, will be calculated. We will analyse the QI coach’s logbook to assign costs to the different tasks performed. Incremental ratios (i.e. change in costs to use the intervention divided by change in the 3rd next available appointment) will also be calculated.

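### A pre-intervention window is stated only for intervention clinics, and the primary model names neither baseline access nor the matching factor, so a controlled change from baseline is not secured

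*Protocol article*

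**What the plan says.** Under Data collection, the article says "Complementary qualitative and quantitative data will be collected over a period of 24 months". It then extends collection by 12 months in the intervention group only and adds "We will collect data from all clinics in the intervention group for at least 3 months prior to the start of the intervention". No sentence gives a pre-intervention window for control clinics.

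Under Data analyses, the primary outcome is to be analysed with a generalised linear mixed model "adjusting for time to account for secular trends as well as important contextual factors such as number of providers and readiness for change". The contrast is described as follows: "Differences between the control and intervention periods and time trends will be estimated using odds ratios and their 95% confidence intervals". The same section plans time series analyses of change since baseline, with T3 as the start of the intervention, and does not restrict them to one group.

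On design, regions are randomly selected for the intervention and clinics in the other regions are controls. "The matching will be based on the clinic level", which reflects registered patients and services offered. Clinics are recruited "using voluntarism and purposeful sampling". Controls receive an audit on access indicators, at a time the article does not give. The sample-size section expresses the target effect as a reduction from the baseline assessment.

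**The concern.** The effect is defined as a change from baseline, so both arms need a baseline taken before anything is done to them. The article commits to that for one arm.

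Imbalance between arms is a real possibility. Whole regions are allocated, the clinics within them volunteer, and matching is on size and services rather than on access. With an ICC of 0.364, stable differences between clinics make up a large part of the error. A baseline in both arms, used in the model, removes the stable part and corrects for chance imbalance. Control data that began only after the audit report would not be a clean baseline.

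There is a smaller issue with readiness for change. It is measured by survey, and the article does not say which measurement enters the model. The Discussion expects the intervention to strengthen local improvement culture. A value measured after the start could therefore absorb part of the effect.

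**Working it through.** **Inputs from the sample-size section:** 24 clinics per arm, 15 professionals per clinic, six time points, ICC ρ = 0.364, cluster-size CV 0.49, mean 11 days, SD 10, d = 0.25, power about 80%.

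**Assumptions (not in the article):** two-sided α = 0.05, in line with the 95% intervals; clinic autocorrelation c from 0.5 to 0.9; provider autocorrelation p from 0 to 0.8.

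**1. The plan's own figure.** Design effect = 1 + [(1 + 0.49²) × 15 − 1] × 0.364 = 7.41. Effective n per arm = 360/7.41 = 48.6. Power at d = 0.25 is 23%, or 27% with equal clusters (design effect 6.10). The stated 80% is not reproduced from the listed inputs. It can be reached with an undisclosed assumption. One example is one baseline plus five follow-ups with a correlation of 0.8 between periods, which gives 79%.

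**2. Chance imbalance.** The standard error of the difference between arms at one time point is 10 × √(2/48.6) = 2.0 days (1.8 with equal clusters), on a mean of 11. This treats clinics as independent. Differences between regions, for which the article gives no figure, would add to it.

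**3. What a baseline in both arms adds (equal cluster sizes).**
- Variance of a clinic-period mean, in SD² units: v = ρ + (1 − ρ)/15 = 0.364 + 0.0424 = 0.4064.
- Correlation of clinic means between periods: r = (0.364c + 0.0424p)/0.4064.
- Variance factor, six follow-ups and no baseline: f₀ = (1 + 5r)/6.
- Variance factor, one baseline and five follow-ups: f₁ = (1 + 4r)/5 − r².
- SE = √(2vf/24); power = Φ(0.25/SE − 1.96).

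Example with c = 0.8 and p = 0: r = 0.2912/0.4064 = 0.717. Without a baseline, f₀ = 0.764, SE = 0.161 and power is 34%. With a baseline, f₁ = 0.260, SE = 0.094 and power is 76%.

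| Clinic autocorrelation | 0 pre + 6 post | 1 pre + 5 post |
|---|---|---|
| 0.5 | 41–46% | 62–64% |
| 0.7 | 34–37% | 69–75% |
| 0.8 | 32–34% | 76–86% |
| 0.9 | 30–32% | 87–98% |

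Ranges are over p = 0 to 0.8.

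**4. Cross-check with CV 0.49.** Five follow-ups, without versus with one baseline, by correlation of clinic means: 36% vs 55% (r = 0.5), 29% vs 66% (0.7), 27% vs 79% (0.8), 25% vs 96% (0.9).

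**5. The larger effect.** The same section also describes the target as a 50% reduction, which is 5.5 days or 0.55 SD at SD 10. With one follow-up and CV 0.49, power is 77% without a baseline. With one it is 88% (r = 0.5), 97% (0.7) or 99% (0.8).

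**The case against.** A reader might infer that controls will have no baseline. The article does not say so. Only the 12-month extension is limited to the intervention group. The quoted sentence counts back from the start of an intervention that controls do not receive during the comparison. On the outcome's source, the article says "No inflation for loss to follow-up is planned because the data is readily obtained from the EMR system for all professionals". This point stands: the control window is unstated, not excluded.

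A reader might also infer that the primary model leaves baseline access out. The named covariates are introduced as examples, and the full list may sit in an analysis plan that is not shown. The contrast between control and intervention periods could bring pre-intervention data in as repeated outcomes. This stands too: the right description is that baseline access is not named. Number of providers may partly stand in for clinic level.

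The comparator with no baseline is also only an illustration. The article does not say whether any of the six time points is pre-intervention, and step 1 shows that a baseline may already be built into the 80%. If so, that is a further reason to secure the baseline in both arms.

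Finally, the article does not say that the intervention targets the readiness score itself. The readiness point is a precaution.

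**Conclusion.** The article fixes a pre-intervention window for one arm and names neither the baseline outcome nor the matching factor in the primary model. It therefore does not secure the controlled change from baseline on which its sample size is expressed. The exposure is a chance imbalance with a standard error of about 2 days on a mean of 11, and a precision gain that may be forgone. At d = 0.25 that gain runs from about 20 percentage points of power at clinic autocorrelation 0.5 to more than 55 at 0.9. It rests on an autocorrelation that the documents do not give, equal cluster sizes and a two-sided 0.05 test.

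It would be tempting to say that most of the power is lost. At d = 0.25 that holds only if clinic differences are highly stable over time. At autocorrelation 0.5 about a third is lost, and at the 5.5-day effect the loss is about 10 to 22 points. Leaving out clinic level has no power cost that can be computed from the documents, and an unmatched analysis of matched clinics is not in itself invalid.

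**What to change.** - State the same EMR extraction window of at least 3 months for control clinics, over the same calendar months as the intervention clinics and before the control audit report is issued.
- Include the baseline third-next-available appointment in the primary model, as a group-by-period contrast or as a baseline mean covariate, together with clinic level.
- Use only pre-intervention values of readiness and number of providers as covariates.
- State the correlation between baseline and follow-up that lies behind the 80% power, if one was assumed.

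The cost is an EMR extraction over the pre-period for 24 control clinics and a few model terms. It should be settled before launch, because past appointment availability may not be recoverable from every EMR later.
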